#### Randomisation

The prescreened cART sites will be assigned by research assistants to the intervention and comparison arms, figure 2, using an electronically generated simple randomisation sequence.

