#### Eligibility criteria

All smartphone-owning HCPs at these sites are eligible including: physicians, medical officers, pharmacists, nurses and midwives, clinical officers, pharmacy technicians and community health workers (lay counsellors and expert clients). Limited rollout showed that 7 in 10 HCPs are smartphone owners. Written informed consent will be sought from eligible HCPs. We expect to enrol 10 HCPs per cART site on average.

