#### Participant timeline

There are 15 regional referral hospitals each with a catchment of ~25 cART sites. Each team of three research assistants requires 4 weeks to enrol HCPs in one regional catchment. Follow-up at each cART site begins after its enrolment and lasts 30 months. The 30-month follow-up period is considered adequate to monitor durability of the real-life impact of the app on ADR reporting. Four additional months will be required to wrap-up the study, thus, 36 months overall (table 1).

**Table 1 T1:** Schedule of enrolment, interventions and assessments

	Study period						
	Baseline	Follow-up schedule					Close-out
Procedures	(t_0_)	t_0_+3 months	t_0_+6 months	t_0_+12 months	t_0_+15 months	t_0_+30 months	t_0_+36 months

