#### Concealment of sequence generation

Using the sealed envelope software, an independent Biostatistician from the Clinical Epidemiology Unit at Makerere University, who will not participate in the subsequent data analyses, generated the simple randomisation sequence.

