#### Blinding

PLHIV, HCPs, PV assessors of the ADR reports submitted to NPC and the biostatistician who will analyse the data will be blinded to the allocation of cART sites. The research assistants will not be blinded to the allocation of cART sites due to the nature of the intervention.

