#### Feasibility and acceptability of the app

Prior to trial implementation, we will conduct a baseline qualitative study to gauge the acceptability and feasibility of introducing the app to HCPs. We will conduct three to five focus group discussions each with five to eight HCPs and 20–30 in-depth interviews in a random 6% of cART-sites (~12) in the intervention arm. During trial implementation, we will document the refusal and failure rates to instal the app among consented HCPs in the intervention arm. App users will be asked to report their experiences to gauge app feasibility, assess user satisfaction and identify potential revisions to the app. We will gauge acceptability of the app based on whether users can recommend the app to other HCPs to report suspected ADRs to NPC.

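### The unblinded research assistants who enrol HCPs also apply the site allocation, and no stated step keeps a site's arm from them until its HCPs are listed, consented and surveyed

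*Protocol article*

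**What the plan says.** All references are to the protocol article.

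- **Who made the sequence.** Under Concealment of sequence generation, an independent biostatistician, "who will not participate in the subsequent data analyses, generated the simple randomisation sequence". The past tense shows that the sequence exists. The section does not say who holds it afterwards or when a site's arm is disclosed.
- **Who applies it.** Under Randomisation: "The prescreened cART sites will be assigned by research assistants to the intervention and comparison arms".
- **Who recruits.** Under Participant timeline: "Each team of three research assistants requires 4 weeks to enrol HCPs in one regional catchment".
- **What recruiters know.** Under Blinding: "The research assistants will not be blinded to the allocation of cART sites due to the nature of the intervention".
- **Who can be recruited.** Under Eligibility criteria: "All smartphone-owning HCPs at these sites are eligible", and "Written informed consent will be sought from eligible HCPs". Ten HCPs per site is an expected average, not a quota.
- **Order of steps.** Table 1 puts eligibility screen, consent and allocation, listed in that order, in the single baseline column. The baseline survey and the qualitative study are in the same column.
- **Qualitative study.** Under Feasibility and acceptability of the app (Data collection): "Prior to trial implementation, we will conduct a baseline qualitative study to gauge the acceptability and feasibility of introducing the app to HCPs". It takes place "in a random 6% of cART-sites (~12) in the intervention arm".

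**The concern.** In a cluster trial with individual recruitment after randomisation, a sound sequence protects the choice of clusters but not the choice of people within them. If the recruiter knows the arm, the set of people enrolled can itself depend on the arm. Here one staff role applies the allocation, knows it and enrols the HCPs.

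The primary outcome is HCP-reported ADRs per 100 000 person-months of treated PLHIV. Training more HCPs, or more motivated ones, can raise the numerator and leaves the denominator unchanged. Intervention HCPs are also trained in paper and web reporting, so a larger or keener group could report more by those routes with no effect of the app. The arm comparison would then mix the effect of the app with the effect of recruitment. The interviewer-administered baseline survey, which is meant to show whether the arms are comparable, could also be taken with the arm known.

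The list of people to approach is not tightly fixed. Eligibility is limited to smartphone owners, yet the Intervention arm section introduces the app to HCPs whether or not they own one. The Comparison arm section has no matching statement on ownership, although it says that training is otherwise identical.

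**Working it through.** **1. Procedure.** The sections on randomisation, timeline and blinding establish by direct statement that research assistants allocate, enrol and are unblinded. When they learn a site's arm is not stated. Table 1's listing order fits consent before allocation but does not require it, because all three steps share one column.

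**2. Sites where early identification is documented.** 6% of 191 intervention sites = 0.06 × 191 = 11.5, matching the article's figure of about 12. That is 12/191 = 6.3% of the intervention arm and 12/382 = 3.1% of all sites. A draw from the intervention arm before trial implementation requires someone to know those sites' arm by then. For the other 370 sites, early knowledge is possible but not documented.

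**3. Room for differential refusal.** Limited rollout covered 629 HCPs at 87 sites (629/87 = 7.2 per site), with refusal of 0% (95% CI 0% to 2%). Put the upper limit wholly in one arm: 0.02 × 7.2 = 0.14 HCP per site, or 2% of HCPs. If reports are proportional to HCPs trained (an assumption), that is 2/25 = 8% of the target effect. Refusal is therefore a minor route. What remains is who is listed and approached, on which the article gives no data.

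**4. Scale, illustration only.** Under the same assumption, one extra HCP per intervention site is 1/10 = 10% at the planned cluster size, or 1/7.2 = 14% at the observed one. That is 10/25 = 40% or 13.9/25 = 56% of the target. The one extra HCP has no source in the article.

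**5. What a given difference would do to the test.** First reproduce the plan's figure: 2 × (1.96 + 0.84)² × 1.179² / 0.25² = 349.1 with unrounded normal quantiles, so 350 per arm. The design effect is 1 + (10 − 1) × 0.25 = 3.25, and 350 × 3.25 / 10 = 113.75, so 114 sites per arm, as stated. (This works only if the 0.25 labelled a coefficient of variation is used as an intracluster correlation.)

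With the same inputs and 191 sites per arm, the standard error of the difference is 1.179 × √(3.25/10) × √(2/191) = 0.069 on a mean of 1.0. The rejection probability at two-sided 5%, with no app effect and a recruitment-driven difference b, is Φ(b/0.069 − 1.96) + Φ(−b/0.069 − 1.96):

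| Assumed difference, % of mean | Probability of a significant result |
|---|---|
| 0 | 5% |
| 2 | 6% |
| 5 | 11% |
| 10 | 31% |
| 15 | 59% |
| 20 | 83% |

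The rows are hypothetical inputs, not estimates. The 2% row is the refusal limit from step 3.

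**6. Sites still open to change.** 382 − 87 = 295, taking the 87 limited-rollout sites as those enrolled when the article was written.

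**The case against.** The case on the other side is substantial.

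- **Silence in a condensed article.** The full protocol may give the order of steps, and so may the flow diagram cited in the Randomisation section, which is not available here. This stands as a limit on what can be concluded about timing. It does not remove the point, because the overlap of allocating, unblinded and recruiting roles is stated outright.
- **Arm known everywhere before recruitment.** A reader might infer this from the existing sequence. The article does not support it. Generation lies with an independent biostatistician, the Blinding section does not say when recruiters learn the arm, and Table 1's order fits consent first.
- **Qualitative-study HCPs discussing the app before consent.** A reader might infer this too. Table 1 places that study in the same baseline column as consent and survey, and nothing says that the recruiting teams run it or are told which sites were drawn. Only the early identification of those sites' arm is documented.
- **Recruitment accounting for 40% to 56% of the target effect.** This is not a finding. It rests on an invented imbalance and an assumed proportionality. Refusal near zero and eligibility of all smartphone owners at a site both narrow the room for it.
- **Existing safeguards.** Sites are prescreened, so the choice of sites is less exposed. The denominator is treated PLHIV, and all ADR reports from the sites are counted. Number and cadres of HCPs and smartphone ownership are compared by arm, with adjusted models if randomisation fails. These limit or could reveal an imbalance but cannot prevent one, and motivation is not among the listed characteristics.

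**Conclusion.** The point holds as a gap in separation between allocation and recruitment. It creates a risk that which HCPs, and how many, are approached and trained differs by arm. The article shows no such imbalance. Early identification of the arm is documented for about 12 of 382 sites; elsewhere it is only not excluded.

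The article's refusal data bound the refusal route at about 2% of HCPs. The listing and approach route cannot be sized from the article. The illustrations assume that reports rise in proportion to HCPs trained, and the test probabilities also assume the plan's SD with a design effect of 3.25. They show only that a modest arm difference would matter for the test.

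Closing the gap is a cheap improvement. The gap is not a reason to regard the design as unsound.

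**What to change.** 1. **Sites not yet enrolled (about 295).** The independent biostatistician keeps the sequence. A site's arm is released to the team only after its list of eligible HCPs has been closed by the same rule in both arms, consents are signed and the baseline survey is complete.
2. **Sites already enrolled (87).** Report the numbers of HCPs eligible, approached, consented and trained, by arm.
3. **Qualitative-study sites (about 12).** Repeat the primary comparison without them as a sensitivity analysis. They were drawn at random within the intervention arm, so leaving them out should not in itself bias the comparison. The standard error rises by a factor of √(1/179 + 1/191) / √(2/191) = 1.017, or about 2%. This checks only those sites and says nothing about recruitment at the rest.

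The cost is a reordering of steps at the enrolment visit and one message per site from the biostatistician. The drawback is that training at a site can be arranged only after its arm is released. Sample size, outcome and primary analysis do not change.

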**Figure 2 F2:**
[figure not shown]
Flow diagram for cluster-randomised trial at full rollout. ADR, adverse drug reaction.

#### Blinding

PLHIV, HCPs, PV assessors of the ADR reports submitted to NPC and the biostatistician who will analyse the data will be blinded to the allocation of cART sites. The research assistants will not be blinded to the allocation of cART sites due to the nature of the intervention.

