**Methods and analysis:**

A pragmatic cluster-randomised controlled trial will be implemented over 30 months at 191 intervention and 191 comparison cART sites to evaluate Med Safety. Using a randomisation sequence generated by the sealed envelope software, we shall randomly assign the 382 prescreened cART sites to the intervention and comparison arms. Each cART site is a cluster that consists of healthcare professionals and PLHIV receiving dolutegravir-based cART and/or isoniazid preventive therapy. Healthcare professionals enrolled in the intervention arm will be trained in the use of mobile-based, paper-based and web-based reporting, while those in the comparison arm will be trained in paper-based and web-based reporting only.

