### Aims and objectives

Our aim is to assess the feasibility, effectiveness, cost and cost-effectiveness of implementing Med Safety for HCP-driven reporting of ADRs associated with DTG containing cART and IPT for TB prevention in PLHIV in Uganda. Our hypothesis is that the use of Med Safety for ADR reporting by HCPs attending to PLHIV on DTG-based cART and/or IPT will increase the ADR reporting rate^21 22^ by at least 25% versus use of existing PV methods alone in 30 months of follow-up at selected cART sites in Uganda. We will test our hypothesis in a pragmatic multicentre open-label cluster-randomised controlled trial whose specific objectives are to:

Assess the feasibility and acceptability of Med Safety for ADR reporting by HCPs at selected cART sites in Uganda.Determine the app’s effect on the rate of ADR reporting versus traditional PV methods alone.Estimate the app’s cost and cost-effectiveness from the provider perspective.

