#### Intervention arm

HCPs at intervention cART-sites will be introduced to the Med Safety mobile app whether they own a smartphone or not. Mobile app, paper form and web form awareness campaigns including initial face-to-face training, posters/brochures and monthly reminder WhatsApp and mobile phone short messages (SMS) for up to 6 months will be undertaken. Training will be conducted by pharmacists from NPC and Makerere University with expertise in PV. The training teams have harmonised the training schedule to ensure uniform training. Interested HCPs with personal smartphones will be invited and assisted to install the mobile app and trained to use it to report suspected ADRs, with emphasis on DTG-linked and IPT-linked ADRs. HCPs will also be trained and encouraged to use traditional PV methods (paper form and web form).

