#### Comparison arm

HCPs at the comparison cART sites will be trained and encouraged to use traditional methods of ADR reporting (paper form and web form). All aspects of the training will be identical to those in the intervention arm except that Med Safety will not be introduced to HCPs in the comparison arm. Reminder WhatsApp and SMS about the paper form and web form will be sent out monthly for up to 6 months.

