#### Outcomes

Our primary outcome is number of HCP-reported ADRs per 100 000 person-months of treated PLHIV per study arm. Our secondary outcomes are number of app ADR reports per 1000 app downloads per month of follow-up; causality (by Naranjo Scale and Liverpool Causality Assessment Tool)^24 25^; seriousness as per the WHO definitions (threatens life, ie, leads to or prolongs hospitalisation, causes incapacitation or death); ADR outcome; cost per ADR report; cost per additional ADR report; and cost per additional avoidable serious ADR report.

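### The plan calls healthcare professionals blinded in an open-label trial, and it does not say how assessor blinding is kept when the reporting channel points to the arm

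*Protocol article*

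**What the plan says.** The Protocol article, under Blinding, says: "PLHIV, HCPs, PV assessors of the ADR reports submitted to NPC and the biostatistician who will analyse the data will be blinded". What these groups are said not to know is the arm of each site. The only exception it gives is: "The research assistants will not be blinded to the allocation of cART sites due to the nature of the intervention".

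Other sections describe the design differently:

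- **Aims and objectives:** "We will test our hypothesis in a pragmatic multicentre open-label cluster-randomised controlled trial".
- **Intervention arm:** "HCPs at intervention cART-sites will be introduced to the Med Safety mobile app whether they own a smartphone or not". Smartphone owners are then helped to install the app and trained to report with it.
- **Comparison arm:** the training is otherwise the same, but "Med Safety will not be introduced to HCPs in the comparison arm".

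The primary outcome is the rate of ADRs that HCPs report. The secondary outcomes include seriousness, "causality (by Naranjo Scale and Liverpool Causality Assessment Tool"), and an incremental cost measure for avoidable serious reports. The cost section also breaks costs down by seriousness, avoidability and causality.

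Two safeguards are described. Under Compliance with allocation, the arm code is added by an officer of the National Pharmacovigilance Centre (NPC) who stands outside routine assessment. Under Quantitative data, the research team receives anonymised data and the randomisation code stays closed until the analysis is done.

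**The concern.** HCPs are both the people intervened on and the people whose reports make up the primary outcome. If the plan says they are blinded, a reader will credit the trial with a protection it lacks and misjudge the risk of bias in its main result.

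The assessors raise a separate question. Causality, seriousness and avoidability are judgements made on each report. A reporting channel that exists by design in one arm can indicate where a report came from. An assessor who sees it, or sees the site name, could grade the two arms differently without intending to. That would affect the secondary outcomes and the cost measures built on them.

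**Working it through.** The plan gives no figure to reproduce on this point. The check is a comparison of sections, group by group, with one short calculation.

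**HCPs.** Blinding lists them as blinded. Aims and objectives calls the trial open-label. Intervention arm and Comparison arm show that the app is introduced at one set of sites and withheld at the other. An HCP who has been shown the app, offered installation and sent reminders about it knows that the site received it. At most, HCPs at comparison sites may be unaware that an app arm exists, and the Blinding section does not say that. The statement and the design cannot both be right.

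**Assessors.** The relevant facts are these:

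1. The app is introduced only at intervention sites, so app reports come from there apart from contamination, which Sample size allows for at about 30%.
2. Data protection says that online data enter VigiFlow and are assessed before they move to VigiBase.
3. Compliance with allocation has the arm coded from the originating site before anonymisation, so the site is identifiable within NPC at that stage.
4. Intervention arm says that NPC pharmacists are among the trainers, so some NPC staff know which sites received the app. Whether any of them also assess reports is not stated.
5. The arm code is kept away from routine assessors. No section says that the channel or the site is.

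**How strongly the channel points to the arm.** Let the intervention arm send N app reports and the comparison arm c × N, with equal numbers of treated patients per arm. Then

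P(intervention | app report) = N / (N + cN) = 1 / (1 + c).

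The document gives no app-report rate by arm, so c is an assumption:

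| c (assumed) | 1 / (1 + c) | Probability |
|---|---|---|
| 0 | 1 / 1.0 | 100% |
| 0.10 | 1 / 1.1 | 91% |
| 0.30 | 1 / 1.3 | 77% |

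The value 0.30 is borrowed from the contamination allowance only for scale. That allowance is not defined as a ratio of app-report rates. Over this range the channel is a strong marker of arm, but not always a certain one.

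**Biostatistician.** Coding by a separate officer, anonymised data and a closed code allow the primary rate to be compared between masked arms, provided the channel is not in the file. Once app-specific outputs are tabulated, such as app reports per 1000 downloads, the coded arm with most of the app reports identifies itself.

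**Outcomes affected.** The primary outcome is a count of reports over person-time and uses no causality, seriousness or avoidability grade. Causality, seriousness and the cost measures that use avoidability do depend on grading.

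**The case against.** The strongest reply has four parts.

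- **The article is condensed.** The masking procedure for assessors may be in the full protocol. This stands in part: the documents do not show that assessors see channel or site, so their loss of blinding is an inference. It does not rescue the HCP statement, which is a positive claim that the same article contradicts.
- **The safeguards are real.** A reader might infer that the whole blinding sentence is false, including for the biostatistician. The documents do not support that. The separate coding officer, the anonymised data and the closed code make masked analysis of the primary rate workable.
- **The channel is not proof of arm.** A reader might infer that every app report reveals its arm. The app is free to download, it had already been launched in limited settings, and the plan itself expects contamination and assesses cross-over. The channel indicates the arm without settling it, and nothing in the documents shows how far or in which direction grades would shift.
- **HCP awareness is inherent.** Knowing that one has a reporting tool is how such an intervention works. This is fair: the fault lies in the description, not in the choice of an open-label design.

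A reader might also infer that biased grading threatens the primary result. It does not, because the primary count needs no grade.

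**Conclusion.** The point holds in three parts of different strength.

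1. **HCPs:** the statement that they are blinded is wrong on the plan's own text. This needs no assumption.
2. **Assessors:** blinding is claimed without a stated means of hiding the channel or the site. The exposure is limited to the judgement-based secondary outcomes and the cost measures derived from them. Its size cannot be calculated from the document. The 77% to 100% range describes how well the channel identifies the arm under assumed rates and equal arms; it does not measure bias in the grades.
3. **Biostatistician:** blinding is workable for the primary comparison and should be claimed for that only.

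This should be corrected. The first part misdescribes the people who generate the primary outcome, and the second can be repaired at modest cost.

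**What to change.** - In the Blinding section, state that HCPs, as well as research assistants, are not blinded. This is a text correction.
- After de-duplication, remove the reporting channel and the site name from the copies of reports used for the trial's causality, seriousness and avoidability grading, and say who does this. De-duplication comes first because matching reports may need those fields.
- Keep the channel out of the analyst's file until the primary masked-arm comparison is locked. Release it afterwards for the app-specific outcomes, and limit the claim of analyst blinding to the primary comparison.

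The cost is a small added data-handling step at NPC, where an officer already codes each report by arm. It could be larger: the plan does not say that this coding comes before routine assessment. If assessment comes first, the trial may have to grade redacted copies separately, and the document does not establish that this needs no extra staff time.
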